## Blinding

Due to the characteristic of exercise intervention, all participants and the aerobic exercise supervisor and *Yi Jin Jing* instructor will not be blinded. But the staff who undertake outcome measuring and statistician who undertakes data processing will be blinded to group allocation.

### Data collection and management

Study-related information, such as participant’s identity, the data collected relating to the study, and medical records, will remain confidential. Case report forms (CRFs) will be completed on paper forms. With regard to self-reported measures, participants will monitor their menstrual cycles using a menstrual diary.

### Data monitoring

The data will be recorded in the CRFs. The CRFs will be filled out truly and accurately. Confidentiality of participants will be protected and guaranteed by storing the hard copies of the data collection forms in locked cabinets in the principal investigator’s office. Access to electronic clinical report forms stored in the excel spreadsheets data file will be password-encrypted and restricted to the principal investigators. The blinded analyst will be provided with a de-identified dataset to preserve confidentiality. This study is supervised by Shanghai University of Sport, and the Office of Postgraduate Affairs of Shanghai University of Sport constitutes the data monitoring committee to monitor and review the data.

### Statistical methods

The intention-to-treat principle will be used in the statistical analysis. We will use multiple imputation, based on 5 replications and a chained equation approach method in the R MI procedure, to account for missing data. Continuous variables will be presented by mean ± standard deviation. We will use the Kolmogorov–Smirnov test to see the normality and Levene test to see homogeneity of variance. Data transformations, such as logarithmic transformation or arcsine square root transformation, will be applied in cases of a non-normal distribution. Analysis of variance (ANOVA) will be used for comparing the differences between groups, and Bonferroni test will be applied if the difference is found to be significant. Paired *t*-test will be used for comparing the differences within groups. Differences between groups of the categorical data (menstrual frequency) will be compared by Kruskal–Wallis test, and Nemenyi test will be applied if the difference is found to be significant. A two-sided *P* value less than 0.05 will be considered significant.

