### Study design

The study is designed as a controlled randomized, superiority trial with three-arm parallel groups. Reporting of the study will follow the Standard Protocol Items: Recommendations for Interventional Trials (SPIRIT) statement (Additional file 1). A total number of 90 diagnosed PCOS patients will be recruited from Yue yang Integrated Chinese and Western Medicine Hospital, Affiliated to Shanghai University of Traditional Chinese Medicine. Patients will be recruited from the gynecologist ward through fliers, posters, and gynecologist recommendations. Patients will be randomly assigned to two intervention and control group with an allocation ratio of 1:1:1. After randomization, the intervention groups will undergo either *Yi Jin Jing* or aerobic exercise training for 12 consecutive weeks and the control group with no training intervention but take oral contraceptives (OCPs). Post-test measurements will be conducted based on the primary and secondary outcomes in comparison to the baseline measures.

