#### Outcome measurements

The primary outcome is serum AMH level. AMH is the best marker of the ovarian function; it could be noticed as a suitable hormonal marker of the ovarian follicular count and as a diagnostic marker for ovarian hyperandrogenism [44–46]. Therefore, we choose AMH as the primary outcome.

Secondary outcomes include:(1). Menstrual frequency.(2). Biochemical profile including FSH, LH, T, E_2_, SHBG, DHEA-S, FAI.(3). Antral follicle count and ovarian volume.(4). BMI(5). HOMA-IR

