#### Sample size

AMH is the target effect, according to a similar research by Moran [47], where the mean AMH level before intervention was 59.1pmoL/L, standard deviation was 20.5pmoL/L, and AMH declined by 13.2pmoL/L in response to exercise. We require 25 participants per group to achieve a power of 80%, two-sided *α* = 0.05. With an approximate attrition rate of 20%, we will recruit 90 participants in total with 30 participants per group.

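### Fixing multiple imputation at 5 replications with about 20% attrition is valid but needlessly noisy: on the planning values, rerunning the imputation changes the p<0.05 verdict of an exercise-versus-control contrast in roughly 9–13% of trials, against about 3% with 50

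*Protocol article*

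**What the plan says.** The protocol article adopts the intention-to-treat principle and says under Statistical methods: "We will use multiple imputation, based on 5 replications and a chained equation approach method in the R MI procedure". The number 5 is a commitment in the text, and no reason is given for it.

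The Sample size section anticipates the amount of missing data: "With an approximate attrition rate of 20%, we will recruit 90 participants in total with 30 participants per group". It takes its planning values from an earlier exercise study: "standard deviation was 20.5pmoL/L, and AMH declined by 13.2pmoL/L in response to exercise". It concludes: "We require 25 participants per group to achieve a power of 80%, two-sided" at α = 0.05.

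Under Outcome measurements, "The primary outcome is serum AMH level". Groups are compared by ANOVA, followed by Bonferroni pairwise tests only if the ANOVA is significant. Significance is a two-sided P below 0.05. The Discussion hypothesises that each exercise arm lowers AMH relative to control, while the Objectives section names aerobic exercise versus Yi Jin Jing as the main comparison.

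**The concern.** Multiple imputation fills each gap with random draws, so its pooled estimate, standard error and p-value shift from one run to the next on identical data. The shift shrinks as the number of imputations grows. With 5 imputations and about a fifth of the post-treatment AMH values missing, it may be large enough to carry a result across 0.05. The plan reads 0.05 as a hard line, and the ANOVA result decides whether pairwise tests are done at all.

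What is at stake is how far the declared result of an exercise-versus-control comparison rests on an arbitrary random draw when more draws would cost almost nothing.

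**Working it through.** **The plan's own figure.** The protocol states no Monte Carlo error for the imputation. Its one computable figure is the sample size. A two-group comparison with its inputs gives

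n = 2 × (1.96 + 0.84)² × (20.5/13.2)² ≈ 2 × 7.85 × 2.41 ≈ 38 per group,

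not 25. The step from 25 to 30 is 25 × 1.2; dividing by 0.8 gives 31.25, so 32. The present point does not depend on the figure of 25.

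**Inputs from the protocol.** 30 per arm, three arms, 5 imputations, 20% attrition, SD 20.5, difference 13.2, two-sided 0.05.

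**Assumed inputs.** Baseline–post correlation 0.3–0.85 (not in the protocol); all attrition becomes missing post-treatment AMH, missing at random; imputation by normal regression on arm and baseline; the 13.2 decline holds as a difference from control.

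**Why the threshold is close.** With 30 × 0.8 = 24 observed per arm, the standard error of a difference is about 20.5 × √(2/24) = 5.92. The expected test statistic is 13.2/5.92 = 2.23, only about 0.27 above 1.96. Simulated power for one contrast at 0.05 is 58–60% with 5 imputations.

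**Size of the noise.** Under Rubin's rules the total variance is T = W + (1 + 1/m)B, and the pooled estimate varies between runs with variance B/m. In the simulations the fraction of missing information was about 0.17 at correlation 0.5. In units of the standard error, the run-to-run SD of the estimate is therefore about

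- m = 5: √(0.17/5) = 0.18
- m = 20: √(0.17/20) = 0.09
- m = 50: √(0.17/50) = 0.06

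The standard error moves as well. The simulated run-to-run SD of the t-statistic is 0.23–0.27 with 5 and 0.07–0.08 with 50. With 5 imputations it is about as large as the 0.27 margin above.

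**Disagreement between two runs on the same data.** Simulated trials were pooled by Rubin's rules with Barnard–Rubin degrees of freedom. Rates are for an exercise-versus-control contrast at the planning effect unless stated.

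| Setting | m = 5 | m = 50 |
|---|---|---|
| 20% missing, correlation 0.3, p<0.05 | 11.3% | 3.6% |
| 20% missing, correlation 0.6, p<0.05 | 10.4% | 2.7% |
| 20% missing, correlation 0.5, range over test variants | 10.4–12.4% | 2.3–3.5% |
| Same, ANOVA first, then Bonferroni | 11.3–11.6% | 3.1–3.5% |
| Overall ANOVA, correlation 0.5 | 11% | 2.5–3.4% |
| 16.7% missing (25 of 30 observed) | 9.6–11.3% | 2.8–3.8% |
| 30% missing | 15–16% | about 4% |
| 10% missing | 6.0–7.4% | about 2% |
| Half the effect (6.6) in both exercise arms, ANOVA first | 4–5% | about 1% |
| No effect | 1–3% | 0.2–1.1% |
| Change scores, correlation 0.85, p<0.05 | 1.5–2.1% | 0.3–0.4% |

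With 20 imputations the rate at p<0.05 is 4.8% at correlation 0.3 and 4.1% at 0.6. At correlation 0.7 single cells lie slightly outside 9–13%: 8.0% for post-treatment values at 0.05, and 14.1% for change scores with the ANOVA step. Further runs without the ANOVA step gave 7–8% at half the effect and 3–4% with no effect.

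**Power.** With the ANOVA step, the gain from 5 to 50 imputations was, for example, 38.8% to 41.5% (post-treatment values, correlation 0.5) and 63.0% to 67.4% (change scores, correlation 0.7), or about 2–4 points.

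**The case against.** The strongest reply is that nothing here is invalid. Rubin's rules allow for a finite number of imputations. A check of a two-arm contrast with 5 imputations and 20% missing gave a type I error of 5.1%, and the power loss is small. A run-to-run SD of about 0.25 in the t-statistic is modest beside a sampling SD of about 1. All of this stands. A reader might infer that the primary analysis is biased or its error rate inflated; neither the documents nor the calculations support that.

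Second, the rate of about one in ten is conditional. It needs a true 13.2 difference on that contrast, and the resulting power of about 60% lies near the point where disagreement is greatest. The 13.2 is a decline in response to exercise, whereas the control arm here takes an active drug. For aerobic exercise versus Yi Jin Jing, the stated main comparison, the rate is about 1–3% if the two are equally effective and about 12% only if they differ by 13.2. This also stands, so the rate must be given as a range.

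Third, a reader might infer that another analyst could not reproduce the result. That goes too far: a recorded seed makes even a 5-imputation run exactly repeatable. The seed and the imputation covariates are details that an article may leave to an analysis plan, so their absence here is no finding. But a seed only fixes which draw is used. It does not reduce how much the verdict depends on that draw.

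None of this answers the central point. The number 5 is stated, not left open, and more imputations gave fewer disagreements in every setting tried.

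**Conclusion.** The point holds as an avoidable loss of precision, not as an invalid analysis. If the planned difference is true for an exercise-versus-control contrast, all 20% attrition becomes missing AMH, and the baseline–post correlation is about 0.3–0.7, the p<0.05 verdict differs between two imputation runs in about 9–13% of trials with 5 imputations, 4–5% with 20 and about 3% with 50. Fewer missing values, a smaller effect, or change scores with a very high correlation bring the 5-imputation rate down to between about 1% and 8%. The correlation is an assumption throughout. The finding is worth acting on because the remedy is nearly free, even where the gain is small.

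**What to change.** In Statistical methods, replace 5 replications with 50 imputations. Twenty is a defensible minimum and gives about 4–5% disagreement in the central settings; 50 brings it to about 3%.

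Record the change in a dated amendment before any unblinded analysis. Recruitment was expected to end in October 2021, so the amendment may come after data collection, and the number must not be chosen after results have been seen.

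The cost is the amendment and trivial computing time for 90 participants. No patients, visits or other parts of the design are affected.

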#### Study measurements

Prior and post to intervention, the following will be measured. Transvaginal ultrasound scan will be performed during the early follicular phase (cycle days 3–5) to document ovary morphology, including antral follicle count and ovarian volume. Fasting blood will be taken for 2–5 days during spontaneous menstrual cycle to check biochemical profiles, including AMH, LH, FSH, T, E_2_, sex hormone binding globulin (SHBG), dehydroepiandrosterone sulfate (DHEA-S), fasting insulin (FINS), and fasting blood glucose (FBG) level. Free androgen index (FAI = T × 100/SHBG) and homeostasis model assessment of insulin resistance (HOMA-IR = FINS × FBG /22.5) will be calculated. All ultrasound and blood tests were performed at the medical laboratory of Yueyang Hospital. All participants will receive a menstrual diary to record menstrual bleedings, menstrual frequency which will be calculated by dividing the number of menstrual bleedings by 3 (ordinal variables: “0,” “1/3,” “2/3,” “1”). Anthropometric indicators including weight, height, and BMI will be measured.

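### An unspecified Kolmogorov–Smirnov pre-test decides whether outcomes are log-transformed, and the arcsine alternative fits none of them; the power cost is small to moderate and falls mainly on secondary outcomes

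*Protocol article*

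**What the plan says.** Under Statistical methods, the protocol article sets out a sequence for continuous outcomes. First come the checks: "We will use the Kolmogorov–Smirnov test to see the normality", together with a Levene test for equal variances. Next comes the consequence: "Data transformations, such as logarithmic transformation or arcsine square root transformation, will be applied in cases of a non-normal distribution". Then comes the comparison: "Analysis of variance (ANOVA) will be used for comparing the differences between groups".

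No outcome has its scale fixed in advance. The section does not say whether the test uses ordinary or Lilliefors critical values. It does not say whether the test is run per arm, on the pooled sample or on residuals, or whether one rejecting arm is enough to transform.

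The outcomes concerned are under Outcome measurements: AMH (primary), FSH, LH, T, E2, SHBG, DHEA-S, FAI, antral follicle count, ovarian volume, BMI and HOMA-IR. Two of these are built from other laboratory values under Study measurements: FAI is T × 100/SHBG, and "homeostasis model assessment of insulin resistance (HOMA-IR = FINS × FBG /22.5) will be calculated". Menstrual frequency is handled separately by Kruskal–Wallis.

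**The concern.** A normality test is a poor switch in a trial of this size. When the mean and SD are estimated from the same sample, the ordinary Kolmogorov–Smirnov critical values are too large and the test rarely rejects. A skewed outcome can pass and go to ANOVA on its raw scale, where a few high values inflate the variance and pull the mean. Ratios and products of positive quantities are natural candidates for a log scale: log FAI = log T + log 100 − log SHBG, and log HOMA-IR = log FINS + log FBG − log 22.5.

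Two further problems do not depend on how skewed the data are. The arcsine square root is defined only from 0 to 1. The section also plans five imputed data sets, which can give different normality verdicts for the same outcome; the rule then yields no single scale on which to pool.

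At stake is some power, mostly on secondary outcomes, and an analysis scale that depends on software defaults and on how the sentence is read.

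**Working it through.** **Inputs.** The plan gives no figure for the pre-test and no spread for any secondary outcome, so there is no figure of its own to reproduce on this point.
- Group size (Sample size): 30 per arm recruited with 20% attrition leaves 30 × 0.8 = 24; the stated requirement is 25. With imputation up to 30 may be analysed.
- AMH (Sample size): "the mean AMH level before intervention was 59.1pmoL/L", with SD 20.5. CV = 20.5/59.1 = 0.347. If log-normal, log-SD = √ln(1 + 0.347²) = 0.34.
- Log-SDs of 0.5 to 0.8 for the skewed secondary outcomes are **assumptions**.

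**Step 1: arcsine.** Its domain is 0 to 1. AMH averages 59.1 and BMI is at least 23 by the inclusion criteria. Hormone levels, FAI, HOMA-IR, follicle count and ovarian volume are not proportions either. The only 0-to-1 variable, menstrual frequency, does not go to ANOVA.

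**Step 2: how often the test rejects.** Simulated log-normal data, 25 per arm, standardised by the sample mean and SD:

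| log-SD | Plain KS, per arm | Plain, any of 3 arms | Plain, pooled (n = 75) | Lilliefors, per arm | Lilliefors, any arm | Shapiro–Wilk, per arm |
|---|---|---|---|---|---|---|
| 0.34 | 0.4% | 1% | 5% | 23% | 54% | 38% |
| 0.5 | 2% | 7% | 25% | 42% | 80% | 64% |
| 0.7 | 10% | 26% | 67% | 65% | 96% | 86% |
| 0.8 | 16% | 40% | 83% | 75% | 99% | 92% |

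Check on the any-arm column, 1 − (1 − p)³: for p = 0.10, 1 − 0.90³ = 27%; for p = 0.16, 1 − 0.84³ = 41%. If all arms must reject, p³ = 0.16³ = 0.4%, so that trigger practically never fires with the plain test.

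**Step 3: raw versus log.** Three-group F test, 24 per arm, two arms reduced by 40%: power is 64% raw against 72% log at log-SD 0.7 (gap 8 points), and 50% against 60% at 0.8 (gap 10 points). These gaps are the loss only if the log is never triggered.

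**Step 4: net loss under the two-stage rule**, in points against always using logs, at log-SD 0.7 to 0.8, 24–25 per arm and a 40% reduction:

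| Reading of the rule | Two arms lower | One arm lower |
|---|---|---|
| Plain, any arm | about 3 | 7–9 |
| Plain, all arms | 8–10 | 16–19 |

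Other readings with two arms lower: plain on the pooled sample or residuals, 0–1.5; Lilliefors with all arms required, about 4; Lilliefors with any arm, about 0.

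A second set-up has 25 per arm, one arm lower and the effect sized for 80% power on the log scale. At log-SD 0.7 and 0.8 the losses are 8.2 and 7.7 (plain, any arm), 15.9 and 20.7 (plain, all arms), 0.1 and 0.0 (Lilliefors, any arm) and 9.4 and 9.3 (Lilliefors, all arms).

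The net any-arm loss is below gap × P(no trigger). At log-SD 0.8 with two arms lower that product is 10 × (1 − 0.40) = 6, against about 3 observed, because the samples that trigger are those where logging helps most.

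**Step 5: AMH.** At log-SD 0.34 the plain any-arm rule loses about 4 points when one arm is lower and about 1 when one arm is higher, which is the two-arms-lower pattern.

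None of these runs includes baseline adjustment.

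**The case against.** A reader might infer that the test almost never rejects, so that strongly skewed outcomes would be analysed raw at a cost of about 10 points. The documents do not support that.
- The low rejection rates hold for the uncorrected test run arm by arm. The article names neither version nor unit, and with Lilliefors values and an any-arm trigger the loss nearly vanishes.
- At strong skew even the plain test fires often: at least one arm rejects in 40% of trials at log-SD 0.8 and in 67% at 1.0.
- The raw-versus-log gap is not the loss under the plan's rule, which logs the samples that are flagged.
- The Discussion hypothesises that both exercise arms do better than control. That is the two-arms-lower pattern, where the plain any-arm loss is only about 3 points.
- With 30 per arm after imputation the test rejects somewhat more often.

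All of this stands and limits the size of the point. It is also fair that an article may leave the test version to an analysis plan, that the arcsine is only an example after the log, and that the statistician is blinded, so the scale cannot easily be steered.

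What remains is what the article does fix: a data-driven trigger for every continuous outcome, and a named remedy that suits none of them. Specifying the test version would reduce the power loss but would leave the scale to be chosen from the data.

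**Conclusion.** The point holds as a minor improvement. The pre-test should not decide the scale, and the arcsine option has no use here.

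The power cost depends on unstated details. It is about 0 to 1 point with Lilliefors values and an any-arm trigger. With the uncorrected test and an any-arm trigger it is about 3 points when two arms are lower and 7 to 9 when one is. If every arm must reject the uncorrected test, it is about 10 to 19 points. The primary outcome is little affected, at about 1 to 4 points.

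The larger figures rest on log-normal outcomes with assumed log-SDs of 0.7 to 0.8 and 24 to 25 per arm, and they concern secondary outcomes for which the article claims no power. They show that skewed outcomes may be analysed raw, not that they will be. The arcsine point needs none of these assumptions.

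**What to change.** Remove the normality test as the trigger. State in advance that named positive, right-skewed laboratory outcomes are analysed on the log scale, adjusted for log baseline, and reported as ratios of geometric means with confidence intervals. The list should hold at least HOMA-IR and FAI, and FINS where it is analysed on its own. Check model residuals by plot, and delete the arcsine square root.

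A fixed scale also gives all five imputed data sets the same model. The cost is about two sentences, which should be settled before the analyst sees outcome data. The small downside is that these effects are read as ratios instead of mean differences.

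### The arms are compared by ANOVA with no baseline covariate; ANCOVA on baseline AMH would be more precise, by an amount that depends on a correlation the protocol does not give

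*Protocol article*

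**What the plan says.** The Statistical methods section gives the between-group method for continuous outcomes: "Analysis of variance (ANOVA) will be used for comparing the differences between groups". Bonferroni comparisons follow if the overall test is significant. A paired t-test "will be used for comparing the differences within groups". Significance is judged at one threshold: "A two-sided *P* value less than 0.05 will be considered significant". No covariate is named, and the section does not say whether the analysed variable is the end-of-treatment value or the change from baseline.

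Baseline values exist by design. Under Study measurements, "Prior and post to intervention, the following will be measured", and the list that follows covers AMH, the other hormones, the metabolic measures, the ovarian ultrasound measures and BMI. Under Outcome measurements, "The primary outcome is serum AMH level".

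The Sample size section describes the earlier study it relies on: the pre-intervention "standard deviation was 20.5pmoL/L", and "AMH declined by 13.2pmoL/L in response to exercise". From these it concludes: "We require 25 participants per group to achieve a power of 80%, two-sided", at alpha 0.05. It mentions neither a correlation between baseline and follow-up nor any adjustment.

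**The concern.** The baseline value of the outcome is usually the best single predictor of its later value. Leaving it out of the model discards information that has already been paid for, and at 25 per arm that matters.

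- If the ANOVA uses end-of-treatment values, baseline is ignored and rho times any chance baseline difference between arms stays in the estimate.
- If it uses changes, baseline is subtracted in full. This over-corrects whenever rho is below 1, and is noisier than post values when rho is below 0.5.
- Since the text allows both, two different primary analyses remain open.

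The within-arm paired tests raise a lesser issue. They do not test a difference between arms, and they absorb time effects and regression to the mean. A result significant in one arm and not in another could be misread as a treatment difference.

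**Working it through.** **Inputs from the protocol.** Difference 13.2 pmol/L and SD 20.5 pmol/L (Sample size), so d = 13.2/20.5 = 0.644. There are 25 evaluable per group and two-sided alpha is 0.05. With three arms there are three pairs, so I take the Bonferroni level as 0.05/3.

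**Assumptions of mine.** The 13.2 is a within-group decline, used here as a nominal difference between two arms. The SD is the same before and after treatment. Rho is not in the protocol, so 0.3 to 0.8 is shown.

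**Step 1: the plan's own figure.** For two independent groups at 80% power, n per group = 2 × (1.960 + 0.842)² × (20.5/13.2)² = 2 × 7.85 × 2.41 = 37.9, so 38 (39 with the t distribution). The stated 25 is not reproduced. A one-sample (paired) calculation with SD 20.5 gives 19 (21 with t), which is not 25 either. A figure near 25 does appear for ANCOVA with rho of about 0.6, but the protocol states no such assumption.

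**Step 2: SD under each analysis.**

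- Post-value ANOVA: 20.5
- Change-score ANOVA: 20.5 × √(2(1 − rho))
- ANCOVA: 20.5 × √(1 − rho²)

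The ANCOVA variance is therefore (1 − rho²) times that of post values and (1 − rho²)/(2(1 − rho)) = (1 + rho)/2 times that of changes. Both ratios are below 1 for any rho strictly between 0 and 1, apart from one degree of freedom.

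**Step 3: power for one pairwise contrast, 25 per group.** The noncentrality is 13.2/(SD × √(2/25)), referred to the t distribution with 48 degrees of freedom. Using the pooled three-arm error degrees of freedom moves the figures by about one point or less.

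| rho (assumed) | Change SD | ANCOVA SD | Post-value, 0.05 | Change, 0.05 | ANCOVA, 0.05 | Post-value, 0.05/3 | ANCOVA, 0.05/3 |
|---|---|---|---|---|---|---|---|
| 0.3 | 24.26 | 19.56 | 61% | 47% | 65% | 43% | 47% |
| 0.5 | 20.50 | 17.75 | 61% | 61% | 73% | 43% | 56% |
| 0.6 | 18.34 | 16.40 | 61% | 70% | 80% | 43% | 64% |
| 0.7 | 15.88 | 14.64 | 61% | 82% | 88% | 43% | 76% |
| 0.8 | 12.97 | 12.30 | 61% | 94% | 96% | 43% | 90% |

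These figures ignore the requirement that the overall F test be significant first, which can only lower them.

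**Step 4: share of the shortfall recovered.** At 0.05 the gap from post-value ANOVA to 80% is 80 − 61 = 19 points. ANCOVA gains 4 points at rho 0.3, 12 at 0.5 and 19 at 0.6, so about a fifth, nearly two thirds and essentially all of the gap. At 0.05/3 the gap is 80 − 43 = 37 points. The gains are 4, 13, 21 and 33 points at rho 0.3, 0.5, 0.6 and 0.7, so about a tenth, a third, just over a half and nine tenths. Power at 0.05/3 passes 80% only between rho 0.7 and 0.8.

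**Step 5: chance imbalance.** The standard error of a baseline difference between two arms is 20.5 × √(2/25) = 5.8 pmol/L, which is 5.8/13.2 = 44% of the target difference. Post-value ANOVA carries rho times the realised imbalance into the estimate; change scores over-correct by (1 − rho) times it.

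**The case against.** Under randomisation, ANOVA on post values or on changes is unbiased and holds its type I error, so nothing here is invalid. That stands: this is a matter of efficiency and of an undeclared choice. Covariate adjustment is often left to a statistical analysis plan, and none is shown. The article does name the model, however, and the model it names has no covariate.

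Three stronger readings are tempting, and the document supports none of them.

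- **That ANCOVA would restore most or all of the missing power.** This needs a value of rho that the protocol does not give. It fails at rho 0.3. At the planned Bonferroni level 80% is not reached even at rho 0.7. The 13.2 is also a decline within an exercise group, whereas the main objective compares two exercise arms and the control is an active drug. The 61% starting point is therefore nominal, and the shortfall itself belongs to the Sample size section.
- **That the plan ignores baseline altogether.** The Study design section speaks of comparing post-test measurements with baseline, which allows change scores. In that case ANCOVA's advantage at 0.05 is about 6 points at rho 0.7 and 2 at rho 0.8.
- **That superiority will be judged from the paired t-tests.** The Statistical methods section gives the between-group comparison to ANOVA and Bonferroni and lists the paired tests separately. The misreading is a reporting risk, not something the protocol commits to.

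**Conclusion.** The point holds as one of precision and specification. The protocol fixes a between-group analysis with no baseline covariate, leaves the analysed variable undefined, and measures baseline in everyone. ANCOVA is more precise than post-value or change-score ANOVA for any rho between 0 and 1, bar one degree of freedom.

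Against post values, the nominal gain at two-sided 0.05 runs from about 4 points (rho 0.3) to about 35 points (rho 0.8). Against change scores it runs from about 18 points down to about 2 over the same range. At 0.05/3, ANCOVA power lies between 47% and 90%. So adjustment recovers much of the shortfall only if rho is about 0.5 or more, and it does not replace a correct sample size calculation. These sizes rest on the assumed rho, equal SDs before and after treatment, and the 13.2 standing in for a between-arm difference. The direction of the conclusion does not depend on the 13.2.

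The paired t-tests are a secondary matter of interpretation. The change should be made, but the planned ANOVA would not give invalid results without it.

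**What to change.** Before unblinding, make these changes to the Statistical methods section:

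- Name as primary analysis an ANCOVA of end-of-treatment AMH on arm with baseline AMH as covariate, both on the log scale if AMH is skewed.
- Report the baseline-adjusted pairwise differences with Bonferroni-adjusted confidence intervals and p-values.
- Use the same model, each with its own baseline, for the continuous secondary outcomes. Menstrual frequency, analysed by Kruskal–Wallis, is not affected.
- Present within-arm change with confidence intervals as description only, not as evidence of superiority.
- If ANCOVA is cited in support of the sample size, state the assumed rho and a range.

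The cost is one degree of freedom and a documented, dated amendment. The article expected recruitment to end in October 2021, so the amendment should record that it was made while the analyst was still blinded. No new patients, visits or measurements are needed.
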